## Abstract

**Background:**

Previous research has shown positive effects of music therapy for people with schizophrenia and other mental disorders. In clinical practice, music therapy is often offered to psychiatric patients with low therapy motivation, but little research exists about this population. The aim of this study is to examine whether resource-oriented music therapy helps psychiatric patients with low therapy motivation to improve negative symptoms and other health-related outcomes. An additional aim of the study is to examine the mechanisms of change through music therapy.

**Methods:**

144 adults with a non-organic mental disorder (ICD-10: F1 to F6) who have low therapy motivation and a willingness to work with music will be randomly assigned to an experimental or a control condition. All participants will receive standard care, and the experimental group will in addition be offered biweekly sessions of music therapy over a period of three months. Outcomes will be measured by a blind assessor before and 1, 3, and 9 months after randomisation.

**Discussion:**

The findings to be expected from this study will fill an important gap in the knowledge of treatment effects for a patient group that does not easily benefit from treatment. The study's close link to clinical practice, as well as its size and comprehensiveness, will make its results well generalisable to clinical practice.

## Background

Music therapy is defined as a systematic process where the therapist helps the client to promote health, using musical experiences and the relationships that develop through them [1]. It is often perceived as a psychotherapeutic method where musical interaction, in addition to verbal discussion, is used as a means of communication and expression. The aim of music therapy is to help people with mental health problems to develop relationships and to address issues they may not be able to by using words alone. Results from a Cochrane review showed that music therapy helps people with schizophrenia to improve their global state, mental state and social functioning in the short to medium term [2]. The review suggested that there is a need for studies examining the effects of music therapy over a longer term. Furthermore, studies are needed to examine the effectiveness of music therapy in clinical practice, and to further explore the psychological 'mechanisms' through which music therapy works.

Music therapy is usually not tailored to a specific diagnosis. Rather, contents of therapy are negotiated with the patient within the process of therapy, based on a variety of individual traits. It has been suggested that factors unrelated to psychiatric diagnosis, specifically therapy motivation, be considered when specifying, prescribing, and evaluating psychotherapy [3]. Psychotherapy may not work if patients are not motivated for it [4-6]. In music therapy, the use of music (i.e. playing or listening to music) itself can often be a motivating factor for patients who may otherwise not be motivated for psychotherapy [7]. Therefore, a low motivation for (other) therapy can become a reason for referral of a patient to music therapy, and such factors may at times be more important than the patient's primary diagnosis. However, there is a scarcity of research addressing the effects of music therapy for patients with low therapy motivation. We found only one randomised study on music therapy for depression where the authors described that the majority of the participants had previously failed to respond to verbal psychotherapy [8].

The problem of low motivation may sometimes be due to a lack of insight and will often lead to poor therapy outcome. It has been described for a variety of disorders, including schizophrenia [9-12], depression and bipolar disorder [11,13], and psychosomatic disorders [14,15]. Music therapy is often recommended for such patients and may have something unique to offer which is worth exploring. A randomised study is needed to examine the potential of music therapy for this under-researched but clinically important population.

Resource-oriented music therapy for people with mental health problems is oriented towards the client's resources, strengths and potentials, rather than primarily on problems and conflicts, and emphasizes collaboration and equal relationships [16,17]. Such a perspective to music therapy builds on a contextual understanding of therapeutic processes [6,18,19], the philosophy of empowerment [20,21], and positive psychology [22]. In music therapy, music may be seen as a central resource for the patient, but a resource-oriented approach will also emphasise the patient's resources in the verbal discussions taking place within the music therapy sessions [17]. Goals of resource-oriented music therapy with people with mental health problems include, among others, the ability to feel and express emotions, to build and sustain relationships to others, and to develop interest and motivation. Therefore the goals of the therapy are closely related to what has been described as negative symptoms in mental health research [2,23].

### Objectives

The objectives of this study are as follows:

1.) To determine whether resource-oriented music therapy helps psychiatric patients who have a low therapy motivation and a willingness to work with music to reduce their level of negative symptoms (primary study outcome).

2.) To determine whether the therapy helps the patients to improve in the following secondary outcomes:

(a) secondary outcomes of general relevance for the patient: general symptoms; general functioning; clinical global impressions.

(b) secondary outcomes specifically linked to the assumed mechanisms of the therapy: interest in music; motivation for change; self-efficacy; self-esteem; vitality; affect regulation; relational competence; actual social relationships.

3.) Provided that significant effects are found: To determine whether general outcomes are mediated by specific outcomes.

## Methods

### Participants

The study will include adult patients with mental disorders who have a low motivation for therapy, as specified below. Criteria for in- and exclusion will be assessed by the ward psychiatrist, based on information collected by the clinical team on the ward.

#### Inclusion criteria

##### (a) Diagnosis F1 to F6

Participants must have a non-organic mental disorder (F1 to F6 according to ICD-10), as assessed by a psychiatrist at a participating centre. The inclusion of such a broad range of mental disorders is based on the finding that mechanisms of psychotherapy are not specifically linked to diagnosis [6]. This broad range of diagnoses will also improve external validity, which is often not optimal in randomised trials which have too narrow inclusion criteria [24].

##### (b) Low therapy motivation

This is the main inclusion criterion for the study. Patients are often referred to music therapy because they have a low therapy motivation and music can be motivating for them. The specific reasons for this low therapy motivation may vary. Some patients may have insufficient insight into having a mental health problem. Others may have insight about having a problem but fail to acknowledge psychosocial components. These patients may demand a 'medication cure' and state that they do not believe in talking. Other patients may state that they do not feel comfortable with talking about emotions and personal problems. Patients may also have low therapy motivation because they did not improve from therapy previously.

##### (c) Willingness to work with music

Participants will be included if they show a willingness to work with music in music therapy. They do not need to have an established interest in music, such as having learnt an instrument or enjoying listening to music, although this may be the case for some of them.

#### Exclusion criteria

##### (a) Severe mental retardation

The outcome measures include some self-reports and therefore participants who are unable to complete these cannot be included. Participants need to be cognitively able to complete a self-report questionnaire.

##### (b) Severe life-threatening somatic illness

Participants with a severe life-threatening somatic illness will not be included because the dynamics of such illness would have such a strong influence on the course of therapy that it would be highly questionable to pool them with other patients.

### Interventions

Participants will be randomly assigned to two groups (details in next section). The interventions for both groups will be provided and monitored over the course of three months from randomisation.

#### Experimental group

##### (a) Music therapy

Participants assigned to the experimental group will receive individual sessions of resource-oriented music therapy. Two sessions per week will be offered, lasting each 45 minutes. Over the course of three months this corresponds to a maximum of 26 sessions. Previous research suggests that at least about 20 sessions are needed for music therapy to have an effect [2]. In cases where it is not possible to provide the maximum number of sessions, therapists should try to ensure that at least 18 sessions will be given within the three-month period. This may be the case when outpatients live too far from the centre to attend two times per week throughout the study period.

Music therapy will be provided in accordance with the principles of resource-oriented music therapy [16,17]. These principles describe general therapeutic attitudes and behaviours (e.g. focusing on the client's strengths and potentials) as well as specific attitudes within the musical interaction (e.g. tuning into the client's musical expression). Attitudes that should be avoided are also described, as well as attitudes that are acceptable but not necessary. Adherence to these principles and competence in their application [16,17,25] will be monitored in two ways. Therapists will rate their own behaviour at the end of every session. This is an efficient way of monitoring the complete course of therapy. To control for a possible subjective bias in these self-reports, randomly selected sessions will be videotaped and the therapist's adherence and competence will be assessed by independent raters. Half of all participants in the experimental group will be randomly selected for videotaping of one therapy session which will also be selected randomly.

##### (b) Standard care

Patients will continue to receive treatment as usual while receiving music therapy. What kind and what dose or frequency of other treatment they receive will be monitored by the ward clinician before randomisation and after 1, 3, and 9 months.

#### Control group

##### (a) Standard care

Patients will receive treatment as usual during the three-month study period. What kind and what dose or frequency of treatment they receive will be monitored by the ward clinician before randomisation and after 1, 3, and 9 months.

##### (b) After the study period: Optional music therapy

For ethical reasons and in order to keep participants in the control group motivated, they will be offered music therapy after the three-month study period. Setting (i.e. individual or group), frequency and duration need not be equivalent to the experimental therapy, but will be set according to clinical needs and possibilities. Adherence and competence will not be monitored.

### Study design

The study will use a single-blind (assessor blinded) randomised design with two parallel groups of equal size. Outcomes will be assessed at pretest (directly after inclusion, before randomisation), at an early intermediate time point (1 month after randomisation), posttest (3 months after randomisation), and six-month follow-up (9 months after randomisation).

The required sample size was calculated for the primary outcome, negative symptoms. We assumed an effect size slightly smaller than medium (f = 0.20, equivalent to d = 0.40), based on the results of our Cochrane Review [2]. For a one-way ANCOVA with one covariate (pretest values), α = 0.05, 80% power, and 36% variance explained by the covariate, the required sample size available for analysis (total number of valid cases) needs to be N = 2 * 65 = 130. In order to allow for 10% drop-outs, the total sample size will need to be N = 144. The actual power of the study may then be greater than 80% because of the additional intermediate assessment points [26].

After inclusion in the study and pretest assessment, the participants will be allocated to conditions using a computerised randomisation procedure, stratified by treatment centre and type of disorder (psychotic versus non-psychotic). This will be done by the principal investigator who has no direct contact to the patients in order to conceal the allocation from the involved clinicians. An overview of the study design is shown in Figure 1.

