### Statistical analyses

The effects of treatment (Objectives 1 and 2) will be analysed using analysis of covariance methods and effect sizes with confidence intervals. Subgroup analyses are planned for psychotic versus non-psychotic disorders. No stopping rules or interim analyses are planned for this study. The primary analysis will be intention-to-treat.

Mediational processes (Objective 3) will be examined using structural equation modelling [42,43], which will address mediation of simultaneous as well as of subsequent change. Factor analysis will be used to examine structures in the adherence and competence ratings.

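### Randomisation is stratified by centre and disorder type, but the only primary-outcome model the protocol names has the pretest as its one covariate; if used for the analysis, its standard errors would be conservative

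*Protocol article*

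**What the plan says.** Three places in the protocol article bear on this.

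- **Study design, randomisation.** After the pretest, patients are allocated by computer, "stratified by treatment centre and type of disorder (psychotic versus non-psychotic"), to "two parallel groups of equal size".
- **Study design, sample size.** The calculation reads "For a one-way ANCOVA with one covariate (pretest values), α = 0.05, 80% power, and 36% variance explained by the covariate", with an effect size of "f = 0.20, equivalent to d = 0.40". It gives 2 × 65 = 130 evaluable patients, and 144 in total after a 10% allowance for drop-out.
- **Statistical analyses.** Treatment effects "will be analysed using analysis of covariance methods and effect sizes with confidence intervals". No covariates are listed. Disorder type returns only as a subgroup variable, and centre does not return.

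So the pretest is the only covariate named anywhere. The text does not say that the strata enter the primary model, and it does not say that they stay out.

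**The concern.** Stratified allocation balances the arms within each stratum. To the extent that balance is achieved, outcome differences between strata drop out of the true sampling error of the treatment difference. A model without stratum terms still counts those differences as residual noise. Its standard error then overstates the uncertainty, confidence intervals are wider than they need be, and the test rejects less often than its nominal 5%.

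The direction is safe, since false positives do not increase. What is at stake is precision that the design has already paid for.

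There is some reason to expect the strata to matter. The article says that the concept of negative symptoms was developed mainly for psychotic disorders. The SANS is rated from an interview, so rater differences could appear as centre differences if raters differ by centre. The article does not say whether they do.

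**Working it through.** **Inputs from the Study design section.** d = 0.40 (f = 0.20); pretest R² = 0.36; α = 0.05, taken as two-sided because only that reproduces N; power 80%; 65 per arm.

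**Assumed input.** q is the share of the residual variance left after the pretest that centre and disorder type together explain. The documents do not give it, so the range 0% to 20% is shown. On the scale of total posttest variance, q = 10% is 0.10 × 0.64 = 6.4%.

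**Step 1: reproduce the plan's figure.** For a two-group ANCOVA with one covariate, f² = 0.04 / (1 − 0.36) = 0.0625. The noncentrality at N = 130 is 130 × 0.0625 = 8.125, with 1 and 127 degrees of freedom. Power is 80.8%. The smallest N that reaches 80% is 128. The stated 130 is therefore sound for the pretest-only model.

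**Step 2: standard error without and with the strata.** The ratio is 1/√(1 − q). Adjusted power uses f² = 0.04 / [0.64 × (1 − q)], with five degrees of freedom assumed for the strata.

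| q (assumed) | SE ratio, unadjusted / adjusted | Adjusted power at N = 130 |
|---|---|---|
| 0% | 1.000 | 80.7% |
| 5% | 1.026 | 82.7% |
| 10% | 1.054 | 84.6% |
| 20% | 1.118 | 88.5% |

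The number of degrees of freedom hardly matters: with ten instead of five, power at q = 10% is still 84.6%.

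**Step 3: actual type I error of the pretest-only test.** With perfect balance within strata, the normal approximation is 2[1 − Φ(1.96 × ratio)]. It gives 4.4% at q = 5%, 3.9% at q = 10% and 2.8% at q = 20%.

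**Step 4: simulation.** It used N = 130, ten assumed strata of 13, near-even allocation within each, and 6,000 runs per setting. The Monte Carlo standard error of a 5% rate is √(0.05 × 0.95 / 6,000) = 0.28 points.

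| q | Type I error, pretest only | Type I error, with strata | Power, pretest only | Power, with strata |
|---|---|---|---|---|
| 0% | 5.8% | 5.6% | 81.3% | 80.6% |
| 5% | 4.6% | 5.1% | 81.2% | 82.3% |
| 10% | 3.7% | 4.6% | 81.1% | 83.6% |
| 20% | 3.1% | 5.4% | 82.8% | 88.0% |

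At q = 0 both models are exact 5% tests, so the rates in the first row are simulation error. They show how far the other rows can be trusted. At q = 10% with no treatment effect, the pretest-only model reported a mean standard error of 0.141, against an actual standard deviation of the estimate of 0.133.

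**Step 5: power forgone.** The fair comparison is between the two models under the same stratified allocation. From the simulation it is 82.3 − 81.2 = 1.1 points at q = 5%, 83.6 − 81.1 = 2.5 points at q = 10%, and 88.0 − 82.8 = 5.2 points at q = 20%. Setting the Step 2 powers against 80.8% would overstate the gain, because stratified allocation slightly helps the pretest-only model too.

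**The case against.** The strongest objection is that the one-covariate ANCOVA belongs to the sample-size paragraph. The analysis section speaks only of covariance methods in general, and the design section itself expects the extra assessment points to raise power above the planned 80%, so the planning model need not be the final one. Leaving the strata out of a power calculation is ordinary and errs on the safe side. A full protocol or SAP, not shown here, may well include them. All of this stands. That the strata are omitted from the final analysis is an inference.

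A reader might also infer that the trial is underpowered or that power is lost. The documents do not support this: the pretest-only model reaches 80.8% at 130. At most a gain is forgone.

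Nor can one say flatly that the intervals are too wide. Pretest SANS already absorbs much of any stable difference by diagnosis, centre or rater, and q could be close to zero. The conservatism also depends on good balance within strata among analysed patients. The article does not describe blocking, some strata may be small, and 10% drop-out is allowed for. With poorer balance, the pretest-only standard error is less conservative than Step 3 suggests.

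What the objection does not remove is that the article sets the stratification beside a pretest-only model, names no other, and nowhere links the strata to the primary analysis. Naming them is a specific improvement with almost no downside.

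**Conclusion.** The point holds conditionally. If the model named for the sample size is also used for the analysis, inference is valid but conservative by an amount that depends on q. Over an assumed q of 0% to 20%, the standard error is 0% to about 12% larger than the adjusted one. Pretest-only type I error falls from 5% to about 3%, and roughly 0 to 5 points of power are forgone. These figures rest on the assumed q, on near-even allocation within strata and, for the simulation, on ten strata. The sample size and its 80% power are correct, and there is no inflation of type I error. This is a modest improvement in specification; it does not correct an invalid analysis.

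**What to change.** State the primary model as an ANCOVA of 3-month SANS on treatment, pretest SANS, treatment centre and disorder type (psychotic or non-psychotic). Add a rule for merging very small centres, fixed before unblinding, and use the same terms for the secondary outcomes, each with its own pretest value. If a full protocol or SAP already says this, the sponsor need only confirm it.

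The cost is a sentence or two and a few of about 127 residual degrees of freedom. Both factors are known for every patient at randomisation, so no new data are needed. If the strata explain nothing, five extra degrees of freedom lower power from 80.8% to 80.7%. The sample size need not change.

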**Figure 1 F1:**
[figure not shown]
**Flow chart of the study design**. *Abbreviations: ***C **– ward clinician; **M **– music therapist; **I **– principal investigator; **A **– blind assessor; MT – music therapy.

The following professionals will be involved in conducting the study and collecting data:

1. Ward clinician **(C)**: the clinician who has the primary responsibility for the patient at the hospital unit.

2. Music therapists **(M)**: academically qualified music therapists with clinical experience in music therapy in psychiatry and specifically trained in the use of the treatment principles for resource-oriented music therapy.

3. Principal investigator **(I)**: The first author (CG).

4. Blind assessor **(A)**: an experienced clinician who is not involved in the daily work at the patient's ward/hospital unit and therefore not aware of the patient's assigned treatment condition. The assessor will have received training in the use of the assessment instruments and will conduct a one-hour patient interview for each assessment. The success of blinding is verified with a separate question in the blind assessor questionnaire.

5. A local co-ordinator will help with the administrative side of the data collection. This person will supervise and facilitate the data collection process and ensure the reliable and timely transferral of information between hospital staff and principal investigator.

6. Other music therapists will assess treatment fidelity (adherence and competence) on the basis of the video recordings.

### Outcomes

The study will use blind ratings as well as self-reports. Standardised instruments with demonstrated validity, reliability and sensitivity to change will be applied whenever possible.

#### Primary outcome: Negative symptoms

The concept of negative symptoms has originally been developed mainly in relation to psychotic disorders but is considered relevant for other mental disorders as well [27,28]. Including affective flattening and blunting, poor social interaction and lack of interest, among others, it is reasonable to assume that processes within music therapy are directly linked to negative symptoms [2]. This outcome will be evaluated by a trained blind assessor using the Scale for the Assessment of Negative Symptoms (SANS) composite score [23]. Validity of the SANS scale has been demonstrated for a variety of mental disorders [27,28]. Interrater reliability, test-retest reliability, internal consistency and sensitivity to change following music therapy have been demonstrated for schizophrenic patients. In order to achieve reliable ratings, the assessor must be trained in the use of this scale.

